### Contamination

Because the experimental-control manipulations are applied across schools that are a considerable distance from each other, and CHWs and parent peers have their own unique designated site, we expect contamination to be minimal. Specifically, all children from the same school and their families will be involved in the same study condition. The distribution of materials is unlikely to influence implementation given that the schools are geographically separated, with limited transportation opportunities in between schools. However, the in-country research team will monitor the extent of any such “seepage” and make statistical adjustments for it, if needed. Monitoring will be established by directly asking facilitators whether any intervention materials were shared with staff/caregivers from other schools every time they complete the delivery of a 16-week intervention and their answers will be carefully documented by the research team (including when, how many people, which materials, and which schools, when relevant). More specifically, this assessment will take place when the research team is in the field to complete the 16-week assessment with caregivers. Again, we do not anticipate contamination given the limited interaction across schools.

### Data collection

Multiple sources of data collection, including Facilitator (F), Caregiver (C), Child (Ch), Research staff (R), and School head (SH) reports, will be used. Following screening (S), data will be collected baseline (T1), 8 weeks (T2; mid intervention) and 16 weeks (T3; post intervention), and 6-month follow-up (T4). All caregiver and child assessments will be available in English and Lugandan (translated using rigorous forward/backward methods). Depending on the existing health surveillance system and resources under the Ministry of Education (MOE) or Ministry of Health (MOH), we will work with ministry stakeholders prior to the scale-up study (during the first 18 months of the capacity-building stage) to determine options to adapt the EBP monitoring systems into school or community service settings. The measurement strategy will be guided by the RE-AIM evaluation framework [100, 101]. The RE-AIM conceptualizes the public health impact of an intervention as a function of five dimensions— reach, effectiveness, adoption, implementation, and maintenance. *Reach*; target populations (CHWs/parent peers, families attending MGFs) will be characterized in terms of demographics, motivation, and child behavior. *Effectiveness*: we will evaluate the impact of MFGs on facilitators, parents, and children. *Adoption:* to characterize the target setting (school/ community clinic), data will be collected at baseline from two sources. *Implementation*; to determine the extent to which the MFG is implemented as planned, checklist-based fidelity monitoring systems have already been designed based on ground breaking work of Schoenwald [102, 103]. Research staff will be trained to used fidelity tools that tap multiple dimensions of a MFG session, including presence and quality of facilitation related to the following: (1) session content; (2) group discussion; (3) use of activities to foster information exchange across families; (4) practice activities within families; (5) summary of learning; (6) explanation of homework; and (7) summary of family strengths. Independent fidelity observations will be conducted by research staff for 20% of MFGs. These data will be used to assess the relationship between planned and actual implementation, to evaluate the integrity of the implementation and how strategies were altered to maximize effectiveness and acceptability. *Maintenance/Sustainment*: We consider three aspects of maintenance: (1) *Implementation maintenance*: we will evaluate CHWs’ and parent peers’ ability to implementing the EBP over time. Facilitators practices during the subsequent implementation cycles (with different groups of families/students) will be measured in each cycle over 2 years via self-report and fidelity observations; (2) *Examine factors that may influence maintenance*: we will systematically examine individual, system level, and other contextual factors that may influence maintenance of the EBP; (3) *System-level sustainability*: to examine sustainability of the EBP within the organizations/sites (from both financial and policy perspectives), we will conduct select qualitative interviews with purposively selected MFG facilitators (*n* = 15 parent peers and *n* = 15 CHWs), school head teachers (*n* = 10) and in-country team members at four time points—baseline, 8 and 16 weeks, and 6-month follow-up. Informants will be purposefully sampled to reflect diversity of schools and perceived level of success in achieving implementation and sustainment of MFGs. Purposeful sampling is used to achieve maximum likelihood of achieving depth of understanding of patterns and processes of implementation and sustainment [104]. Interview guides will consist of semi-structured questions relating to experience with implementing and integration the MFG [105, 106]. Participants will also be asked to provide a narrative account of efforts to implement the MFG, including barriers and facilitators experienced. Table 3 lists the quantitative data collection tools, constructs, informant, and timing.

**Table 3 Tab3:** Measures

Instruments	Reporter	Timing
Aim 1. To examine the short- (8 and 16 weeks) and long-term (6-month) outcomes (primary outcomes) associated with the Multiple Family Group (MFG)		
1. Disruptive Behavior Disorder Rating Scale [121]	C	S
2. Iowa Connors and Impairment Scales [122, 123]	C	S, T2, T3, T4
3. Alabama Parenting Questionnaire (APQ)-short form [124]	C, Ch	T1, T2, T3, T4
4. Parent Stress Index-short form [125]	C	T1, T2, T3, T4
5. Brief Symptom Checklist-short form [126]	C	T1, T2, T3, T4
6. Strengths and Difficulties Questionnaire [127]	C	T1, T2, T3, T4
7. Family Relations and Cohesion scale (adapted from Parent Child Relationship Inventory, Child Caregiver Communication Scale, Family Assessment Measure, and Family Adaptability and Cohesion Scale) [10–13, 65–71]	C	T1, T2, T3, T4
8. Within-family support subscale from Family Assessment Measure [10–13, 65–71]	Ch	T1, T2, T3, T4
9. Multidimensional Students’ Life Satisfaction Scale [128]	Ch	T1, T2, T3, T4
10. Parenting Practices Survey (PPS) [10–13, 65–71]	Ch	T1, T2, T3, T4
11. Behavior in School [10–13, 65–71]	C	T1, T2, T3, T4
12. Personal Health Questionnaire [10–13, 65–71]	Ch	T1, T2, T3, T4
13. Child Depression Inventory (CDI-short form) [129]	Ch	T1, T2, T3, T4
14. Tennessee Self-Concept Scale [130]	Ch	
Aim 2. To examine the uptake, implementation, fidelity, and sustainment of two MFG implementation approaches.		
4. Knowledge, Skill, Attitude Test (KSAT) for MFG facilitators [131]	F	T1
5. Attendance logs	F	every MFG session
6. MFG Intervention Fidelity Assessment [131]	F, C, R	every MFG session for F & C, every other session for R
7. Implementation and Feasibility Assessment [131]	F, SH	T2, T3, T4 for F; T3 for SH
8. Program Sustainability Assessment [132]	F, SH	T2, T3, T4 for F; T3 for SH
Aim 3. To elucidate multi-level factors that influences uptake, implementation, sustainment, and youth outcomes.		
MACS process measures [131]	F	T2, T3, T4
Qualitative interviews	F, SH	T3

Key: Facilitator (F), Caregiver (C), Child (Ch), Research staff (R), and School head (SH)

Screening (S), baseline (T1), 8 weeks (T2; mid intervention), 16 weeks (T3; post intervention), and 6-month follow-up (T4)

### Data analysis plan

#### Qualitative data analysis

All qualitative interviews will be digitally recorded and transcribed. Interviewers will then compare transcripts with digital records to insure accuracy of transcription. All field notes, interview transcripts, and interviewer notes summarizing interviews will be entered into NVivo [107]. Accuracy of information will be assessed through triangulation in which accounts of specific events and behaviors obtained from field notes, interviews, surveys, and archival material are compared [108]. To insure credibility of findings and enhance the validity and reliability of data, all interviews will be reviewed by at least two members of the research team. Consensus on coding and coding procedures and modifications to coding books will occur through regular team meetings. Study results will be presented to informants, enabling them to provide comment of results and suggest modifications or additional avenues of investigation.

Using a methodology of “Coding Consensus, Co-occurrence, and Comparison” [109], implementation team logs and interview transcripts will be analyzed in the following manner. Each investigator will review this material to develop a broad understanding of content as it relates to the project’s specific aims and to identify topics of discussion and observation. Investigators will prepare short descriptive statements or “memos” to document initial impressions of topics and themes and their relationships and to define the boundaries of specific codes (i.e., the inclusion and exclusion criteria for assigning a specific code) [110]. The empirical material contained in the field notes and interview transcripts will then be independently coded by the project investigators to condense the data into analyzable units. Segments of text ranging from a phrase to several paragraphs will be assigned codes based on a priori (i.e., from the interview guide) or emergent themes (also known as open coding) [111]. Following the open-coding, codes will be assigned to describe connections between categories and between categories and subcategories (also known as axial coding) [111]. Codes will also be assigned to material to reflect the social and demographic characteristics of study participants. Lists of codes developed by each investigator will be matched and integrated into a single codebook.

Five transcripts will be independently coded by at least two investigators. Disagreements in assignment or description of codes will be resolved through discussion between investigators and enhanced definition of codes. The final list of codes or codebook, constructed through a consensus of team members, will consist of a numbered list of themes, issues, accounts of behaviors, and opinions that relate to coalition structure, function, development, and sustainment. With the final coding structure, two investigators will separately review a sample of transcripts to determine level of agreement in the codes applied. A level of agreement ranging from 66 to 97%, depending on level of coding (general, intermediate, specific), indicates good reliability in qualitative research [112].

Upon completion of the coding of the remaining transcripts, NVivo will be used to generate a series of categories arranged in a treelike structure connecting text segments grouped into separate categories of codes or “nodes.” These nodes and trees will be used to further the process of axial or pattern coding to examine the association between different a priori and emergent categories. They will also be used in selective coding of material to identify the existence of new, previously unrecognized categories. The number of times these categories occur together, either as duplicate codes assigned to the same text or as codes assigned to adjacent texts in the same conversation, will be recorded, and specific examples of co-occurrence illustrated with transcripts. Through the process of constantly comparing categories with each other, the different categories will be further condensed into broad themes.

#### Quantitative data management and analyses

*Exploratory scale structure analysis*. The research will use robust estimators (in the form of Huber-White estimation) to accommodate non-normality and variance heterogeneity. We will conduct formal tests of outliers and be sensitive to specification error. Inter-item reliability analyses for all scales will be conducted using confirmatory factor analytic (CFA) perspectives; correlations across time and construct will be examined*Data-reduction procedures*. Most of the proposed instruments have summary scoring procedures; however, multiple scores in specific domains may result in multicollinearity, requiring further data reduction. Various data-reduction strategies will be conducted, including factor analyses with oblique rotation [113] and Chi-squared Automatic Interaction Detector (CHAID) algorithms, to identify the strongest variables in the pool. The Exhaustive CHAID method, developed by Biggs, deVille and Suen [114] will be used to explore various groups of predictor variables as they relate to outcomes*Tests of sample equivalence across study conditions*. We will use baseline data to examine potential biases related to possible attrition by condition or selection biases not addressed by random assignment. Preliminary analyses will be performed to compare the schools, facilitators, and adult caregivers in the three study conditions on descriptive/clinical characteristics at baseline to ensure that randomization succeeded. Any ancillary variables that are not the focus of hypotheses, but relate meaningfully to outcomes within treatment groups are candidates for inclusion as covariates. When covariates differentiate treatment groups, they will be included in all analyses to remove confounding effects*General statistical considerations*. To address *aims # 1 and 2*, we will use random-effects models to examine scores over the four assessments. Random-effects models have characteristics that provide solutions to commonly observed problems in the analysis of longitudinal data; missing data, serial correlation, and time-varying covariates [114]. These analyses can model systematic person-specific deviations from the average time trend. Just as the nesting of participants within providers is an example of multi-level data, the nesting of perspectives within teacher reports can also be viewed as multi-level data. By treating treatment perspective as a “repeated measurement” we can estimate the difference between the three conditions on outcomes as a synthesis of the three perspectives. Divergence between the perspectives can also be examined by including interactions between covariates, condition and the rater effect. We will model each outcome as a function of group, time and group-by-time interaction. We will use Supermix software for the mixed-effects linear regression [96].To address aim 3, our analyses will use variants of structural equation modeling (SEM) with Mplus. The models we test often will be statistically over-identified. We will evaluate model fit using both global fit indices (e.g., relative/normed chi-square *χ*^2^/df with range 2.0–5.0) [115, 116], comparative fit index (CFI) (with value ≥ 0.95) [117], standardized root mean square residual (RMR (below 0.08) [117], root mean square error of approximation (RMSEA) (with the lower limit is close to 0 and the upper limit less than 0.07) [118] and indices of fit that are diagnostic of specific points of ill fit in the model (e.g., standardized residuals, modification indices). If poor model fit, then we will examine diagnostics that suggest revisions to the model that are meaningful and that will significantly improve model fit.Hypotheses testing

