##### Parent peers and CHWs to facilitate the adapted MFG

At each of the school sites assigned to the parent-peer-delivered condition (*n* = 10), the head of school and the Chair of the Parents Teachers Association (PTA) will identify up to six parent peers to receive the training to deliver the adapted MFG. Parent peers will have already received some training for their current roles (e.g., workshops in methods to reach out to parents whose children are not performing well in school or not attending; facilitation skills in relation to organizing parent meetings). We expect to recruit 60 parent peers from the 10 schools in the parent-delivered condition.

At each of the school sites assigned to the CHW-delivered condition (*n* = 10), we will collaborate with the village local leaders, the district health officials, and the Ministry of Health (MOH) to identify up to 60 existing outreach workers associated with local primary care clinics in the study area. CHWs have already received training in health assessment, home and school outreach and facilitation of health-related meetings. Many of the CHWs are also local leaders within their communities. We expect to recruit 60 community health outreach workers to deliver the adapted MFG to children from 10 schools assigned to their condition.

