#### Statistical power calculations

The present research uses multi-level structural equation modeling (MSEM) as opposed to traditional multi-level modeling (MLM) because of the presence of mediation [87]. The two are closely related, but the former is primarily available in the Mplus computer software. Power computations in MSEM models are complex because of the large number of assumptions about population parameters that must be made [87–89]. One approach is to power the study based on limited information estimation strategies that focuses on the most sample size demanding equation in the broader system of equations [90]. For longitudinal MLM studies, this also requires taking into account the potential presence of correlated errors of measurements, person-specific effects, and dropout [91–95]. Hedeker and Gibbons [96] also provide a power analysis approach that allows for specification of anticipated attrition patterns and correlations among the repeated observations. Power analyses for a linear trend over time take into account: (1) four measurement time points; (2) a three-group design; (3) a random effect for time and a random effect for facilitator within school for provider-type hypotheses; (4) a residual autocorrelation of rho = .3 and; and (5) an 8% attrition rate between successive time points. Randomization is at the school level. For the hypotheses involving children nested within facilitators or schools, our sample size calculations also incorporate recommendations outlined in Donner et al. [97], and allow for an inflation factor such that our effective sample size is two thirds that of the actual sample size. Table 1 presents detectable effect size (a between group difference increasing linearly from 0 at baseline to effect size measured in standard deviation (SD) units at the last time point) corresponding to 80% power.

**Table 1 Tab1:** Power analysis

Unit (*n* per group)	4 time points	Effect size
School (*n* = 30)	0.39	moderate
Facilitators (*n* = 120)	0.28	moderate
Family (*n* = 3000)	0.10	small

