### Aim 2. To compare the uptake and implementation of MFGs by trained family peers and CHWs

#### Hypothesis

Given the level of training that CHWs receive prior to the study, they will evidence higher-fidelity initially, yet with training and ongoing supervision, we expect these differences to decrease over time.

To evaluate the fidelity, quality of implementation for MFGs implemented by family peers and CHWs, we will carry out a series of descriptive analyses and examine level of fidelity in four domains (described above). We will examine fidelity by year first to understand any change patterns over time, and then will combine analyses across years if no meaningful differences are found. Finally, see random-effects modeling to be used to examine differences by implementers over time.

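### Facilitators, who are not randomised, are placed in the randomisation check and its covariate rule, which can adjust away part of the peer-versus-CHW contrast, chiefly initial fidelity in Aim 2

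*Protocol article*

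**What the plan says.** All references are to the protocol article.

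- **Balance check** (Quantitative data management and analyses, item on sample equivalence). Preliminary analyses will "compare the schools, facilitators, and adult caregivers in the three study conditions on descriptive/clinical characteristics at baseline to ensure that randomization succeeded".
- **Candidate covariates** (same item). "Any ancillary variables that are not the focus of hypotheses, but relate meaningfully to outcomes within treatment groups are candidates for inclusion as covariates".
- **Inclusion rule** (same item). "When covariates differentiate treatment groups, they will be included in all analyses to remove confounding effects".
- **Unit of allocation** (Statistical power calculations). "Randomization is at the school level".
- **Source of facilitators** (Parent peers and CHWs to facilitate the adapted MFG). At schools assigned to the peer arm, "the head of school and the Chair of the Parents Teachers Association (PTA) will identify up to six parent peers". For the CHW arm, the team works with village leaders, district health officials and the health ministry to "identify up to 60 existing outreach workers associated with local primary care clinics in the study area". Of the latter group the section adds: "Many of the CHWs are also local leaders within their communities".
- **Aim 2 hypothesis.** "Given the level of training that CHWs receive prior to the study, they will evidence higher-fidelity initially", with the gap expected to narrow under training and supervision.
- **Conceptual model** (Contextual influences on implementation and scale-up). Delivery by peers or by CHWs is assumed to act through provider-level influences (path b), which carry through to families and then to child outcomes. Aim 3 models facilitator variables at level 2 of the mediation structure.

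**The concern.** A baseline comparison can bear on randomisation only for units that were randomised, or that existed and were identified independently of the allocation. Facilitators meet neither condition. They are recruited because of the arm their school was given, and from a pool that defines that arm. A difference in background between peers and CHWs is expected under perfect randomisation.

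The next step matters more. Treating such a difference as confounding and adjusting for it changes the question. The second study objective and the Aim 1 ordering hypothesis compare delivery by actual parent peers with delivery by actual CHWs. After adjustment for facilitator background, the contrast compares peers and CHWs of equal background. A real difference between the two task-shifting options could then be reported as smaller than it is. The article's own conceptual model places provider-level variables on the pathway, so the equivalence item conflicts with that model.

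**Working it through.** The plan gives no figure to reproduce. The first two steps need no assumptions; the other three are partly or wholly illustrative.

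**1. Can the check be carried out as stated?** The check names three conditions. The facilitator recruitment and program delivery sections describe 60 parent peers and 60 CHWs in the two MFG arms. The comparison condition is printed materials, and no facilitator is described for it. A three-condition comparison of facilitators is therefore not possible.

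**2. Can the covariate enter all analyses?** Aim 1 models child outcomes over three conditions. A facilitator covariate is undefined for 1000 of 3000 dyads, one third. It could enter only a model restricted to the two MFG arms.

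**3. How easily would a facilitator trait be flagged?** Assume a two-sided 5% test, 60 v 60, independent facilitators, and a trait that differs by d SD. Then power ≈ Φ(d·√(60/2) − 1.96).

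| d (SD) | d·√30 − 1.96 | Chance flagged |
|---|---|---|
| 0.25 | −0.59 | 28% |
| 0.5 | 0.78 | 78% |
| 0.8 | 2.42 | 99% |
| 1.0 | 3.52 | about 100% |

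These are chances of detecting a difference, not of adjusting for it. The trait must also pass the filter on candidate covariates.

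**4. What does adjustment do to a single-level contrast?** Let the true peer-versus-CHW difference be T and let the covariate carry a share s of it. The adjusted contrast is T(1 − s). Take T = 0.50 SD (assumed):
- s = 25%: 0.50 × 0.75 = 0.375; simulated 0.37 to 0.38.
- s = 50%: 0.50 × 0.50 = 0.25; simulated 0.24 to 0.25.
- s = 100%: 0; simulated about 0.

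The simulation used 4000 runs per setting, d from 0.5 to 1.5, and no school clustering. Unadjusted estimates stayed at about 0.50. The document gives no value for T, s or d.

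**5. Which planned effects are exposed?** The effect of primary interest in Aim 1 is condition by trajectory. A time-constant covariate entered as a main effect shifts levels, not group-by-time slopes. A small longitudinal simulation (60 v 60, four visits, a trait 1 SD apart carrying the whole gap, 60 runs) gave:

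| Quantity | Unadjusted | Main effect added | Trait-by-time added |
|---|---|---|---|
| Group-by-time slope | −0.126 | −0.126 | −0.01 |
| Initial-level difference | 0.47 | 0.13 | – |

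With about 15% of later visits missing, the slope was −0.130 both with and without the main effect. The exact initial-level figure depends on the variance components assumed; the pattern does not. The rule does not call for covariate-by-time terms, but the Aim 1 text allows trajectory variation to be modelled later on constant and time-varying covariates. The Aim 2 hypothesis concerns the initial level of fidelity, which is the term that main-effect adjustment changes.

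**The case against.** The strongest defence has four parts.

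- **The rule has a filter.** A difference alone does not trigger inclusion. Candidates must be ancillary, must not be the focus of a hypothesis, and must relate to outcome within groups. This stands. It arguably spares prior training, which the Aim 2 hypothesis names, and one can argue that it spares other provider-level variables on path b. It does not clearly spare general traits such as education, experience or a leadership role. The outcome-related condition also tends to select the traits whose adjustment moves the contrast.
- **The primary effect is an interaction.** A reader might infer that the primary child-outcome test in Aim 1 is biased. The document does not support that. A main-effect covariate leaves group-by-time essentially unchanged, and a facilitator covariate cannot be used in the three-arm model at all.
- **The item has a second purpose.** It also mentions selection biases that random assignment does not address, and facilitators are hand-picked. Describing them by arm is therefore useful. That supports description, not a claim about randomisation and not adjustment for confounding.
- **Covariate lists belong in the SAP, and an adjusted contrast can be informative.** Both are fair. The point here is not a missing list but a rule that the article states and that cannot hold for facilitators as written. A labelled secondary adjusted estimate is acceptable.

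**Conclusion.** The text is wrong as written; the severity is minor to moderate. Three things follow from the document alone: facilitator differences are no evidence about randomisation, the three-condition facilitator comparison cannot be made, and a facilitator covariate cannot enter the three-arm Aim 1 model.

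The risk to the peer-versus-CHW contrast is real but conditional. It needs a facilitator trait that is measured, differs between the arms, relates to outcome and passes the filter. It then falls chiefly on Aim 2's initial fidelity level, and on slopes only if covariate-by-time terms are added. The loss equals the share of the contrast that the trait carries, which the document does not allow one to quantify. A reader might infer that the rule erases the provider contrast. That is only the extreme case, in which the covariate carries all of it. The 0.25 SD and zero results rest on an assumed 0.50 SD difference and assumed shares.

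**What to change.** In the sample-equivalence item of the quantitative analysis section:

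1. Limit the randomisation check and the covariate-inclusion rule to baseline characteristics of schools, children and caregivers.
2. State that facilitator characteristics are described by MFG arm only, with no inference about randomisation.
3. State that the main Aim 1 and Aim 2 arm contrasts are reported without facilitator covariates.
4. Use facilitator characteristics in the Aim 3 mediation models or in a clearly labelled secondary adjusted analysis of the two MFG arms.

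The cost is a few sentences in the analysis plan. No new data are needed, and design and sample size do not change.
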